Randomisation for the study will be conducted at the seminar level, with each seminar class being randomised according to the scheme outlined in Fig. 1. The randomisation process will be conducted by an independent party to ensure unbiased allocation, using coin-flip or computer-generated randomisation procedures, to determine to which condition (Condition 1 or Condition 2; Cluster Types A and B, respectively) each class is assigned, while a rule is implemented so that, if a given instructor teaches multiple classes in one semester, the difference in the number of classes assigned to Cluster Type A vs. Cluster Type B does not exceed one. Our main comparison focuses on the randomised arms (Cluster Types A and B). Additional non-randomised comparison classes (Condition 3, Cluster Type C) will be included only if a given seminar cannot be randomised due to scheduling or instructor constraints. These observational data serve as ancillary information but will not be part of the main randomisation-based analysis.

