### Data analyses

Data collection for the main study phase will be used for the main data analyses, which will be conducted once main data collection has terminated.

Descriptive statistics will be used to summarise the baseline characteristics of the study sample, including measures of central tendency (e.g., mean, median) and dispersion (e.g., standard deviation, interquartile range), as appropriate given the distribution of each variable. These summaries will provide an overview of participant demographics and initial conditions across intervention groups.

For the main effect analyses, mixed-effects models will be employed. Between-class comparisons will be made, accounting for clustering at the class level. If indicated, models will include fixed effects for intervention and period, as well as random effects for semester, classes and participants, as appropriate.

Both intent-to-train (ITT) and per-protocol analyses will be conducted to ensure robustness and comprehensive interpretation of the results. The ITT analysis will include all participants as randomised, regardless of adherence to the intervention, while the per-protocol analysis will focus on data related to periods in which the participant completed the exercises as intended.

Appropriate covariates, such as baseline scores and relevant demographic factors, will be included in the models to adjust for potential confounding. Statistical significance will be set at the alpha level 0.05, and results will be reported with 95% confidence intervals to convey the precision of the estimates.

To minimise missing data, we are employing online data collection, which facilitates real-time entry and immediate correction of inconsistencies, enhancing data completeness. Additionally, we are implementing mixed models in our statistical analyses, which effectively handle missing data by using all available data points to estimate model parameters.

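### Allocation is balanced within instructor, but the stated model has no instructor term, so the standard error can be too large where instructors are split across arms and too small in some realised allocations

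*Protocol article*

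**What the plan says.** On allocation, the section on participants, recruitment, randomisation and sample size sets the unit: "Randomisation for the study will be conducted at the seminar level". The mechanism is described as "using coin-flip or computer-generated randomisation procedures". An instructor condition follows: "a rule is implemented so that, if a given instructor teaches multiple classes in one semester". The limit that it imposes for such an instructor is that "the difference in the number of classes assigned to Cluster Type A vs. Cluster Type B does not exceed one". Two same-semester classes of one instructor are therefore always split 1:1, and three go 2:1. No restriction is stated for an instructor with one class per semester, or across the two semesters.

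On analysis, the Data analyses section plans between-class comparisons "accounting for clustering at the class level". The terms are then listed, subject to need: "models will include fixed effects for intervention and period, as well as random effects for semester, classes and participants, as appropriate". On adjustment it says: "Appropriate covariates, such as baseline scores and relevant demographic factors, will be included in the models". Instructor appears neither among the model terms nor among the example covariates.

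**The concern.** The design treats instructor as important enough to constrain allocation, and the model then treats all classes of one instructor as independent. Students of the same instructor plausibly share teaching quality and style, so those classes are correlated.

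The effect depends on where the classes fall. If an instructor has one class in each arm, the instructor effect cancels from the treatment difference, but a class-only model leaves it in the error term. The test is then conservative and loses power that the design had secured. If an instructor has two classes in the same arm, they carry less information than two independent classes, and the class-only error is too small. With about 10 classes there is little power to spare. An unspecified instructor term also leaves room to choose between models after the data are seen.

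**Working it through.** **Inputs from the protocol.** At least 50 participants per condition; at least 10 seminars over two semesters; alpha 0.05; a z-standardised change score, so total variance is set to 1. I take 10 classes of 10 students, five per arm. The seminar count may include non-randomised classes.

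**Inputs assumed.** Instructor variance s_i = 0.02-0.10, class variance s_c = 0.02-0.05, residual s_e = 1 − s_i − s_c, and d = 0.5 for a medium effect. The protocol gives no variance, intraclass correlation, number of instructors or classes per instructor.

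**The plan's own figure.** No power is stated for 50 per condition, so there is nothing to reproduce. For scale, ignoring clustering: 0.5/√(2/50) = 2.5, and 2.5 − 1.96 = 0.54, which gives 70.5% power (two-sided). The point does not depend on this.

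Let v = s_c + s_e/10, the variance of a class mean apart from the instructor effect. The class-only analysis compares class means on 8 degrees of freedom, which matches a balanced mixed model with a random class intercept.

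**(a) Five instructors, one class in each arm.** True variance of the difference: 2v/5. Variance the class-only model expects: 2(s_i + v)/5. Ratio of standard errors: √((s_i + v)/v). For s_i = 0.05 and s_c = 0.02, v = 0.02 + 0.093 = 0.113 and the ratio is √(0.163/0.113) = 1.20. Type I error and power are simulated. The last column adds fixed instructor effects, leaving 4 degrees of freedom.

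| s_i | s_c | SE ratio | Type I, class only | Power, class only | Power, fixed instructor |
|---|---|---|---|---|---|
| 0.02 | 0.02 | 1.08 | 3.7% | 47% | 42% |
| 0.05 | 0.02 | 1.20 | 2.6% | 40% | 43% |
| 0.05 | 0.05 | 1.17 | 2.9% | 35% | 37% |
| 0.10 | 0.02 | 1.39 | 1.5% | 31% | 45% |
| 0.10 | 0.05 | 1.32 | 1.8% | 27% | 38% |

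**(b) Same arm in both semesters.** In each arm, two instructors have two classes each and one has a single class. True variance of an arm mean: s_i(4 + 4 + 1)/25 + v/5 = 0.36 s_i + v/5. Expected within-arm variance of class means: v + s_i(5 − 9/5)/4 = v + 0.8 s_i. For s_i = 0.05 and s_c = 0.02, the model SE is √(2 × 0.153/5) = 0.247 and the true value is √(2 × 0.0406) = 0.285, a ratio of 0.87. For s_i = 0.02 / 0.05 / 0.10 the ratios are 0.93 / 0.87 / 0.81, and simulated type I error is 6.4% / 8.1% / 10.3%.

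**(c) Ten instructors, one class each.** The class intercept absorbs the instructor effect: ratio 1.00, type I error about 5%.

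**(d) Averaging over allocations.** Five instructors with one class per semester, independent coin flips, leaving out draws with fewer than two classes in an arm: type I error 4.9% at s_i = 0.05 and 5.3% at 0.10 (s_c = 0.02).

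**(e) Random instructor intercept in layout (a).** With s_i = 0.05-0.10, the instructor variance is estimated as zero in 17-31% of simulated trials. Type I error is 5.4-6.3% when the degrees of freedom (4 or 8) follow the fit, and 8.5-8.9% when 8 are always used.

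**The case against.** The strongest reply is that the model text is provisional: it is hedged, the covariate list is open, and a condensed article may leave the exact random-effects structure to an analysis plan. That would answer silence, but the article is not silent. It names the clustering level and lists the random effects. The hedge qualifies the terms listed, and the covariates are there to address confounding, not the error structure that restricted allocation creates. The reply does lower the weight of the point: nothing in the text forbids an instructor term.

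A reader might go further and infer that the standard errors are simply wrong, or that the test is liberal whenever instructors are not split. The documents do not support either reading. Any error needs instructors with several randomised classes and a non-zero instructor variance, and neither is stated. An instructor with one class is also not split, yet causes no error. The too-small case needs two or more classes of one instructor in one arm. Within a semester the rule largely prevents this (three classes still go 2:1), so it arises mainly across semesters. It is also conditional on the draw: over coin flips the rate is near 5%. Conditional validity still matters, because only one allocation will be analysed.

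Two further objections stand. The direct consequence of the rule is conservative, so it threatens power and not false-positive control. And the remedy is not free: fixed instructor effects halve the degrees of freedom and lose power when instructor variance is small.

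**Conclusion.** The concern holds in conditional form. The stated model omits the factor used to restrict allocation. If instructors teach several randomised classes and differ from one another, the standard error is 17-39% too large where they are split across arms, with type I error of 1.5-2.9% and reduced power, under assumed instructor variance 0.05-0.10 and class variance 0.02-0.05. For a realised allocation that puts an instructor in the same arm in both semesters it can be too small: 8.1-10.3% type I error in layout (b) for instructor variance 0.05-0.10 and class variance 0.02. That is a property of an unfavourable draw, not of the procedure on average. With one class per instructor the stated model is correct. All sizes rest on 10 equal classes of 10 and on variance shares that the protocol does not give. The change is worth making before analysis, but the point does not show that the trial's inference is invalid.

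**What to change.** In Data analyses, name instructor in the primary model as a random intercept, with classes nested in instructor. Specify a small-sample degrees-of-freedom correction such as Kenward-Roger or Satterthwaite; without one, the random-intercept model is itself too liberal with this few instructors. Enter semester as a fixed effect instead of a random one, since the balancing rule works per semester and there are only two. Use the same structure for the secondary outcomes. State that the instructor term is dropped if every instructor turns out to teach a single randomised class, because it then cannot be separated from the class effect.

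Fixed instructor effects should not be the default with about 10 classes. They take 8 degrees of freedom to 4, lower power from about 47% to 42% at instructor variance 0.02, and cannot be fitted if every instructor stays within one arm.

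The text change is a few sentences and needs no new data, because instructor identity must be known to apply the rule. The price is fewer class-level degrees of freedom and a modest power loss if instructor variance proves small.

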During times where Condition 2 (first comparator, TAU only) is active, participants will attend the standard communication skills seminar, which includes not-AI-enhanced communication skills exercises. This condition will be implemented for the full duration of the seminar within the semester lecture period, with participants getting no specific access to AI tools or related prompts outlined in Condition 1.

Participants undergoing Condition 3 (second, non-randomised comparator, TAU only) will attend communication skills seminar with instructions and exercises comparable to those in Condition 2. This Condition will serve as an observational, non-randomised control to compare against condition 1, but not be part of the main analyses. It is added due to procedural reasons in cases where randomisation of a seminar to Conditions 1 or 2 is not feasible. This may occur for example if certain classes already began instruction before randomisation could take place or if they are run by instructors who cannot accommodate the required arrangement. Such classes serve as an additional, observational comparator to explore potential baseline or contextual differences. We will address these differences by adjusting for key covariates (e.g., baseline skill levels) in the analyses.

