### Participants, recruitment, randomisation procedures, and sample size estimates

Recruitment for this study will target students enrolled in the communication skill seminar (*Seminar Gesprächsführung*) as part of the Bachelor of Science in Psychology program at a German university.

Inclusion criteria for study participants are as follows: 1) Being enrolled as student in the communication skill seminar (Seminar *Gesprächsführung*, A3), which is part of the Bachelor of Science in Psychology program; 2) Participating in one of the seminars from summer-term 2025 up to winter-term 2025/2026; 3) At least 18 years of age; 4) Sufficient proficiency in the German language to participate (as the seminar is conducted in German, this is implicitly given, as German language proficiency is required for course participation). There are no additional exclusion criteria for this study.

Recruitment for the main study begins summer-term 2025 up to winter-term 2025/2026. Participants will be informed about the study by the seminar teachers. Students will be encouraged to participate voluntarily, with informed consent required for enrolment. Reminder messages will be sent out to maintain interest and promote participation throughout the study duration.

The timeline for participant enrolment, interventions, and assessments is as follows: Enrolment begins early during each semester/course, where students provide informed consent. We provide the current informed consent forms (for classes randomised to Conditions 1 and 2 and one for classes in Condition 3) as additional file 1. Allocation occurs at the start of the course (t0), followed by the baseline assessments. The end of the course (t1) includes final assessments. Data close-out for each semester occurs after t1 with optional group discussions. Final data close-out will occur following the last semester during which new data are collected, and any follow-up assessments are completed.

With regard to target sample size, our goal is to enrol at least 50 participants per condition to ensure robust statistical power for detecting medium effect sizes, allow stratified analyses, and to enhance the generalisability of our findings. During the two semesters contributing to the main study, we anticipate recruiting participants from at least 10 seminars.

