### Allocation concealment/blinding

The blinding strategy for this study includes rater blinding to maintain the integrity of the data and minimise bias. Given the nature of the study, it is not feasible to blind participants to the type of intervention. Raters responsible for evaluating communication skills exercises and correctness of free-text responses will be blinded to the condition to which the participants were assigned. In circumstances where unblinding becomes necessary (e.g., unforeseen technical issues or procedural clarifications), a strict protocol will be followed to disclose the intervention assignment in a controlled manner.

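### Type C status need not be settled before a sibling class's arm is known, so if an instructor's classes are drawn one at a time, a foreseen AI class could leave the randomised comparison

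*Protocol article*

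**What the plan says.** Four statements in the protocol article bear on this.

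- **Unit and device** (Participants, recruitment, randomisation procedures, and sample size estimates): "Randomisation for the study will be conducted at the seminar level". An independent party does this, "using coin-flip or computer-generated randomisation procedures".
- **Instructor cap** (same section): the rule limits imbalance within an instructor ("if a given instructor teaches multiple classes in one semester, the difference in the number of classes assigned to Cluster Type A vs. Cluster Type") to one class.
- **Timing** (same section): "Allocation occurs at the start of the course (t0), followed by the baseline assessments".
- **Route to Type C**: the same section says that non-randomised classes "will be included only if a given seminar cannot be randomised due to scheduling or instructor constraints". The description of Condition 3 under Study design gives examples: "if certain classes already began instruction before randomisation could take place or if they are run by instructors who cannot accommodate the required arrangement". These are introduced as examples, so the list is not closed. Type C classes are taught as usual, comparably to Condition 2, and stay out of the main analysis.

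The Data analyses section keeps everyone as randomised in the intention-to-treat (ITT) analysis. At least 10 seminars are anticipated over two semesters. The number of classes per instructor is not stated.

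**The concern.** Each rule is reasonable alone. The difficulty lies in their combination. A cap of one makes part of an instructor's allocation deducible once an earlier part is known. An independent party cannot conceal a result that the published rule already gives away. The instructor teaches the first class and so knows its arm.

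If the second class has not yet been declared randomisable or Type C at that point, the decision can be taken with its arm in view. The incentive would probably run one way. Type C is the same teaching as Condition 2, so a class foreseen as control gains nothing by leaving, whereas an instructor reluctant to run the AI exercises might report being unable to accommodate the arrangement.

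The AI classes that remain could then be a selected set. ITT cannot repair this, because a class declared non-randomisable was never randomised. With about 10 classes, each one carries roughly a tenth of the randomised evidence.

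**Working it through.** The plan gives no figure to reproduce here. The check has three parts.

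**1. What the cap makes predictable.** Input: a difference of at most one per instructor per semester. Permitted A/B sequences were enumerated, taking each as equally likely where the cap applies to the semester total.

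| Classes per instructor | Cap on semester total | Cap held after every draw |
|---|---|---|
| 2 | AB, BA only: second class certain | second class certain |
| 3 | 6 of 8 sequences: second class guessed correctly 67% of the time, third fixed in 1/3 of cases | second class certain, third free |
| 4 | 6 sequences: third fixed in 1/3 of cases, fourth certain | second and fourth certain |

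Only for two classes is the second class fixed under both readings.

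**2. How many AI classes could be foreseen.** Assume k two-class instructors, each drawn sequentially. The second class is AI with probability 1/2, so:

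- expected foreseeable AI classes = k/2, which is 0.5 for k = 1 and 2.5 for k = 5;
- chance of at least one = 1 − 0.5^k, which is 50% for k = 1 and 97% for k = 5.

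**3. Possible bias and loss of power.** All inputs except the 10 classes are assumptions. Class effects have SD = √ICC in units of the total SD. In the worst case, every foreseen AI class with a below-average class effect goes to Type C. The expected number lost is k × 1/2 × 1/2 = k/4. That takes the AI arm from 5 classes to 4.5 (k = 2) or 3.75 (k = 5). Simulation of 100,000 trials per setting gave this upward bias in the AI effect (SD units):

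| ICC | k = 2 | k = 5 |
|---|---|---|
| 0.05 | 0.019 | 0.060 |
| 0.10 | 0.026 | 0.084 |
| 0.20 | 0.038 | 0.120 |

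For scale, take 5 v 5 classes of 10 students. The standard error is √[(2/5)(ICC + (1 − ICC)/10)]:

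- ICC 0.05: √(0.4 × 0.145) = 0.24;
- ICC 0.20: √(0.4 × 0.28) = 0.33.

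The largest biases are thus about 0.25 (0.060/0.24) to 0.36 (0.120/0.33) of a standard error.

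Power of a class-level t-test (assumed d = 0.5, 10 per class):

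| ICC | 5 v 5 | 4 v 5 | 3 v 5 |
|---|---|---|---|
| 0.02 | 0.525 | 0.465 | 0.389 |
| 0.05 | 0.447 | 0.394 | 0.329 |
| 0.10 | 0.359 | 0.316 | 0.264 |

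Losing one AI class costs 4 to 6 points, and losing two costs about 10 to 14.

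**The case against.** A reader might infer that the protocol prescribes class-by-class drawing. It does not. A cap defined over a semester's classes fits a joint draw equally well, and if an instructor's classes are drawn and released together, nothing is foreseeable. The start-of-course timing is one line in a general timeline. The example of a class that began before randomisation is also compatible with a single common draw.

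A reader might also infer that Type C is a free exit. The text restricts it to seminars that cannot be randomised, and nothing permits moving a class already assigned. Separate consent forms for randomised and Condition 3 classes mean that status is settled by the time a class's students consent. Diverting a class because of its expected arm would misapply the rule.

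The bias figures need the same caution. They assume that instructors divert classes with poor prospects, whereas the likelier motive is reluctance to run AI. In the model used, exit unrelated to the class effect produces no bias, only lost power.

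Finally, this is a journal article, and some operational detail may stand in a fuller document. The silence of the Allocation concealment/blinding section on how class allocations are concealed is not counted as an error here.

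These points limit the finding but do not remove it. No passage requires a joint draw, and the consent forms do not stop an instructor knowing a sibling class's arm before a later class's status is settled. The article itself states the timing, the cap and the Type C route, and together they leave the gap.

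**Conclusion.** The point holds conditionally. If an instructor's classes are drawn one after another, the second class of a two-class instructor is certain in advance. With three or more classes, which later classes are fixed or favoured depends on how the cap is read. Because Type C status need not precede knowledge of a sibling's arm, a class foreseen as AI could leave the comparison before ITT applies.

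The documents support an unclosed route, not planned or likely misuse. The real size of any bias is unknown. The range of about 0.02 to 0.12 SD rests on assumed pairing (2 to 5 two-class instructors), an assumed ICC of 0.05 to 0.20, and diversion of every foreseen AI class with below-average prospects. It is a modest risk that is worth closing because doing so is cheap.

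**What to change.** Amend the description of Condition 3 under Study design and the section on participants, recruitment and randomisation:

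1. Before the first class of each semester starts, close a dated list of all seminars. Mark each as randomise or Type C with the reason, having first asked each instructor whether they can run either arm.
2. The independent party allocates all classes marked randomise in one computer draw, choosing at random among allocations that satisfy the existing instructor cap, and releases all results together. This replaces allocation at the start of each course.
3. State that a class listed as randomise cannot later become Type C, and that it stays in its drawn arm for ITT even if the AI exercises are not delivered.

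Each class then has a probability of 1/2 of being AI when its eligibility is decided. For the second of two classes, the chance of a correct guess falls from 100% to 50%. The cap, the independent party and the already permitted computer procedure all stay.

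The cost is a wording amendment and earlier administration. Seminars must be listed and instructors asked before the semester, and a class added late goes to Type C by default.
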